**Figure 1 f1:**
[figure not shown]
Flowchart of the study design.

**Control group:** placebo + conventional treatment (including radiotherapy) group,

**Intervention group:** personalized tumor peptide vaccine + conventional treatment (including radiotherapy) group,

Subjects will be stratified according to different cancer types and first, second, and third-line treatment stages based on individual condition assessment, and then randomly enter two cohorts in a 1:1 ratio. In addition, there is a one-way crossover experiment (cross-over design) during the research process. Cross-over to the investigational treatment arm (peptide vaccine plus radiotherapy) will be permitted only for patients in the control group who demonstrate radiologically confirmed disease progression, as assessed by RECIST 1.1 and verified by the investigator. Eligibility for cross-over requires that patients meet predefined safety and clinical criteria, including an ECOG performance status of ≤2, absence of Grade ≥3 adverse events, and adequate hematologic, hepatic, and renal function. The proportion, timing, and reasons for cross-over will be systematically recorded and transparently reported. The intervention group will undergo the second phase of personalized tumor peptide vaccine group plus conventional treatment (including radiotherapy), and the response rate of the two phases will be evaluated before and after crossover. In both cohorts, all subjects received radiotherapy, and radiotherapy doses will be further divided into low and high doses. This design will allow us to answer questions about vaccination efficacy and the impact of various radiation doses.

For patients who want to enroll in neoantigen clinical trials, screening for neoantigens may be recommended. It is necessary to take the patient’s fresh tumor tissue (surgery or biopsy or cerebrospinal fluid, pleural effusion, ascites, etc.), and perform whole-exome and whole- transcriptome sequencing on peripheral blood for further clinical development of individualized targeted treatment plans. At the same time, these test data can be used for personalized tumor neoantigen screening in this study. Peptide vaccine therapy requires an 8-week preparation period for the preparation of the peptide vaccine, during which patients continue to maintain standard treatment.

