Patients entering the control group’s conventional treatment (including radiotherapy) group will receive conventional treatment plus radiotherapy. Radiotherapy is divided into low-dose and high-dose (first phase); until disease progression occurs, patients can choose to “cross groups” and receive individual treatment. The second stage of treatment consists of tumor peptide vaccine plus radiotherapy (no harm from treatment in the early stage). Patients entering the intervention group ‘s individualized tumor peptide vaccine + conventional treatment (including radiotherapy) group will complete three precise radiotherapy sessions before initiating vaccination with the peptide vaccine. The peptide vaccine treatment will be carried out one week after the end of radiotherapy. The peptide vaccine treatment will last for 5 months. It is a course of treatment until the treatment discontinuation event specified in the protocol occurs. Subjects will continue to undergo post-treatment safety visits, survival follow-ups and tumor progression follow-ups after finishing treatment.

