### Sample size calculation

2.8

This sample size was approximated based on 20% differences between two groups, at 80% detection power.

Calculation method: The primary purpose of this study is to prove that the vaccine treatment group is more effective than the placebo (standard care), with PFS as the main efficacy evaluation index, the planned enrollment time is 24 months, and all subjects are evenly enrolled in the study. The follow-up time is 12 months. According to previous research, it is assumed that the median PFS of the traditional treatment (the control group) is 4 months, and the median PFS of the vaccine group is 10 months (13). The design of crossover of patients who failed in group 1 to group 2 does not affect the statistical results of PFS of the main study. It is based on the PFS before crossover as the statistical calculation.

The 6th month is selected as the interim analysis time node. Considering 0.1 loss to follow-up, 40 patients need to be recruited, with an average of 20 people in each group (**Table 2**). Through the interim analysis, we can make a preliminary validity judgment on the main purpose of this study to determine whether to continue recruiting more patients.

**Table 2 T2:** Sample size calculation for an interim analysis using log rank tests.

Look	Time	–Sample size–		—————Events—————				—Cum.subject time—	
		Group1	Group2	Group1	% of S.S.	Group2	% of S.S.	Group1	Group2
1	6.0	19.2	19.3	6.2	32.1	3.5	18.0	35.6	41.1
2	12.0	38.3	38.5	17.0	44.5	10.4	27.2	98.0	122.8
3	18.0	57.5	57.7	28.7	50.0	18.6	32.2	166.0	217.3
4	24.0	77.0	77.0	40.7	52.9	27.1	35.2	234.9	316.0
5	30.0	77.0	77.0	46.5	60.5	32.3	41.9	268.2	375.1
6	36.0	77.0	77.0	47.7	61.9	33.9	44.0	274.4	393.7

Considering that this study is aimed at pan-tumor and the results of previous studies are based on small samples of liver cancer, we made 4 hypotheticals median PFS prediction values for statistical analysis. The final median PFS was 4 months in the control group and 8 months in the neoantigen vaccine group. The two groups will be enrolled in a 1:1 ratio, α=0.025 (two-sided), β=0.2, and at least 154 subjects with 77 subjects each group are required and the research power reached 80% (**Table 3**).

**Table 3 T3:** Total sample size calculation.

Power	N1	N2	N	Haz ratio (HR)	Ctrl med surv time (M1)	Trt med surv time (M2)	Accrual pat’n	Accrual time/total time	Ctrl loss	Trt loss	Ctrl to trt	Trt to ctrl	Alpha	Beta

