### Statistical methods and data analysis

2.9

1. The results of this experiment mainly use statistical description methods. The measurement data lists the mean, standard deviation, median, maximum value, and minimum value, and the technical data and grade data list the frequency, rate, and confidence interval.2. All statistical analysis will be performed using SPSS software.3. Safety analysis: Mainly descriptive statistical analysis, analyzing adverse events, serious adverse events and adverse reactions of each group of people. Adverse reactions are defined as “definitely related/possibly related, unable to determine” related to this clinical trial.4. Survival Analysis: Progression-free survival (PFS), the primary endpoint of this study, will be analyzed based solely on data collected prior to cross-over, thereby preserving the integrity and statistical power of the comparison between neoantigen and placebo groups. The Kaplan-Meier method will be used to estimate the median PFS and calculate 95% confidence intervals. Group differences will be compared using the log-rank test. Overall survival (OS), as a secondary endpoint, will be estimated using Kaplan-Meier curves and log-rank tests. To account for potential bias introduced by the cross-over design, we will apply the rank preserving structural failure time (RPSFT) and two-stage methods, as well as inverse probability of censoring weighting (IPCW) to adjust for treatment switching. Additionally, adjusted OS analyses will be conducted by matching patients who cross over with comparable patients in the vaccine group based on key baseline factors (e.g., cancer type, age, performance status), using propensity score matching or multivariable Cox proportional hazards modeling. Sensitivity analyses will include intention-to-treat (ITT), per-protocol, and as-treated populations. Subjects will be stratified according to cancer type and first, second, and third-line treatment stages based on individual condition assessments, ensuring that these factors are appropriately considered in the analysis. Additionally, in the multivariable Cox proportional hazards model for both PFS and OS, cancer type will be included as a covariate, along with other relevant baseline factors, to control for potential confounding effects.5. Other Effectiveness analysis: Estimate the objective response rate (ORR), disease control rate (DCR) and other efficacy endpoints and improve the 95% confidence interval. The interval estimation uses the Clopper-Pearson method. The effect of lab correlates such as RT dose on clinical outcomes of response and time-to-event will be estimated using logistic regression and Cox mode respectively. The longitudinal data such as quality of life will be estimated using mixed-effect model.6. Tumor neoantigens response analysis: Neoantigen-specific responses are evaluated by ELISPOT, flow cytometry, and TCR-seq. Peptide–MHC tetramers enrich specific T cells for scRNA/TCR-seq analysis in PBMCs and tumor tissue (if available). TCR clonotype dynamics, ctDNA, and epitope spreading are monitored over time. IHC/mIHC is used to assess immune microenvironment changes when biopsy samples are available.

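### As ordinarily defined, the as-treated PFS sensitivity analysis favours the vaccine even if it is inactive, because the first dose follows a waiting period that patients must pass event-free

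*Protocol article*

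**What the plan says.** The survival item of section 2.9 covers both PFS and OS. PFS, the primary endpoint, is compared between the neoantigen and placebo groups on data before crossover, with Kaplan-Meier estimates and a log-rank test. OS is adjusted for switching by RPSFT, two-stage and IPCW methods, and crossed-over patients are also to be matched on baseline factors with vaccine-arm patients. The item then states: "Sensitivity analyses will include intention-to-treat (ITT), per-protocol, and as-treated populations". It gives no rule for placing time before the first vaccination.

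The design separates randomisation from vaccination in two ways:
- **Vaccine arm.** Radiotherapy takes 1 week (section 2.3.1), and section 2.2 adds: "The peptide vaccine treatment will be carried out one week after the end of radiotherapy". Section 2.2 also says "Peptide vaccine therapy requires an 8-week preparation period for the preparation of the peptide vaccine", without tying that period to randomisation.
- **Control arm.** Vaccine is available only after radiologically confirmed progression, and only with ECOG 2 or less, no Grade 3 or higher adverse event and adequate organ function (section 2.2).

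**The concern.** A vaccine-arm patient counts as vaccinated only after reaching the first dose. If those who progress earlier are not dosed, a fixed as-treated grouping moves their early events to the unvaccinated group and credits the survivors' waiting time to the vaccine. This is guarantee-time (immortal-time) bias. Restricting PFS to data before crossover does not prevent it, because it arises before the first dose and not from switching.

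A sensitivity analysis is meant to show whether the primary result is robust. One that favours the vaccine when the vaccine does nothing could seem to confirm a chance PFS finding or to contradict a correct null one.

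**Working it through.** **Plan's own figures.** The inputs are from section 2.8: "α=0.025 (two-sided), β=0.2, and at least 154 subjects with 77 subjects each group are required"; PFS medians of 4 against 8 months (HR 0.50); equal allocation; uniform accrual over 24 months with 12 months of follow-up; and 0.10 loss.
- Schoenfeld events: 4 × (2.241 + 0.842)² / (ln 0.5)² = 79.1.
- With exponential PFS and 10% loss per month, expected events at 77 per arm are 47.6 and 34.0 (Table 2: 47.7 and 33.9).
- The mean event probability is (47.6 + 34.0)/154 = 0.530, so N = 79.1/0.530, about 149 (Table 3: 153). The design is reproduced within 3%.

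**Share progressing before the first dose.** Take a 4-month PFS median in both arms (inactive vaccine). Two weeks is 0.46 month and ten weeks is 2.30 months.
- 2 weeks: 1 − 0.5^(0.46/4) = 7.7%, or 5.9 of 77.
- 10 weeks (1 week radiotherapy, 1 week gap, 8 weeks preparation after randomisation): 1 − 0.5^(2.30/4) = 32.9%, or 25.3 of 77.

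**Crude rate ratio by hand, ignoring censoring.** Mean PFS is 4/ln 2 = 5.77 months. Assume nobody who progresses before the first dose is vaccinated. Patients who reach that dose at time v then have mean PFS v + 5.77.
- Per-protocol, dropping early progressors from the vaccine arm only: 5.77/6.23 = 0.93 at 2 weeks; 5.77/8.07 = 0.72 at 10 weeks.
- As-treated at 2 weeks: the unvaccinated group has 77 + 5.9 = 82.9 events in 77 × 5.77 + 5.9 × 0.23 = 445.7 patient-months, a rate of 0.186. The vaccinated rate is 1/6.23 = 0.160. The ratio is 0.86.
- As-treated at 10 weeks: 77 + 25.3 = 102.3 events in 77 × 5.77 + 25.3 × 1.07 = 471.5 patient-months, a rate of 0.217. The vaccinated rate is 1/8.07 = 0.124. The ratio is 0.57.

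The values 0.23 and 1.07 are mean times to progression among those progressing before v: 5.77 − v·S/(1−S), with S = 0.5^(v/4).

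**Simulation.** Inactive vaccine, 77 per arm, 1,500 trials per setting, two-sided 0.025, so 1.25% false positives are expected in the vaccine's favour. Loss was 0 to 1% per month.

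| PFS analysis | 2-week wait | 10-week wait |
|---|---|---|
| As-treated, fixed groups | HR 0.85–0.86, about 9% (8–12% across runs) | HR 0.54–0.56, about 90% |
| Per-protocol, vaccine arm only trimmed | HR 0.92, 4% | HR 0.67–0.69, 41–44% |

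With a common landmark in both arms, HR is 0.99–1.02 with 1.0–1.5% false positives. With time-dependent vaccination, HR is 1.00–1.02 with 0.3–1.3%. A per-protocol rule applied alike to both arms gives HR 0.99–1.01 with 0.9–1.8%.

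**OS.** The documents give no post-progression survival, so these are ranges under assumptions.
- Base case (first dose and crossover delay about 0.5 month, 70% of progressing controls willing and fit, post-progression median 6 months): as-treated HR 0.71. Most variations of it gave 0.47–0.86.
- At 90% immediate crossover, with no wait in the vaccine arm, the HR was 0.99. It reversed when every progressor switched at once.
- With the 10% monthly loss that Table 2 implies and no fitness selection, it was 0.98–1.72 at 50–90% crossover.
- Per-protocol OS gave HR 0.79 when crossovers were excluded, but 1.24 when they were censored at crossover.
- Time-dependent vaccination gave OS HR 1.02–1.36 under the null, because crossover follows progression. It is not a sound repair for OS.

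**The case against.** The strongest reply is that the article defines neither set. Such definitions are commonly left to the full protocol or SAP, and their absence is no fault. That stands, so a reader should not infer that the plan already forms groups by later vaccination. What remains is that the article names an as-treated analysis whose ordinary form misleads in this design.

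Four stronger readings are also tempting, and the documents do not support them:
- **The 10-week figures describe this trial.** They need randomisation to precede preparation, which is not stated. Inclusion criterion 7 also admits patients whose peptides are already prepared.
- **Every early progressor goes unvaccinated.** Section 2.4.3 does not list progression among its numbered reasons for stopping, and the follow-up section describes no scan before the first dose. If half of early progressors were still vaccinated (an assumption), as-treated false positives would be about 4% at 2 weeks and 25% at 10 weeks.
- **Per-protocol is biased by construction.** The control arm is described as receiving placebo, so a symmetric rule is possible and would be unbiased. Section 2.2 sets out no placebo dosing, so symmetry is not assured either.
- **As-treated OS must favour the vaccine.** The ranges above show otherwise.

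The sentence on sensitivity analyses also follows the OS switching text, so its application to PFS is a reading of the item, though the item covers both endpoints. Finally, these are sensitivity analyses. The primary PFS comparison is between the neoantigen and placebo groups, and the planned switching methods address OS.

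**Conclusion.** The point holds in a limited form. If as-treated carries its usual meaning and patients who progress before the first dose are not vaccinated, as-treated PFS would show HR about 0.86 for an inactive vaccine at the 2-week wait, with about 9% false positives against 1.25%. About 0.55 is an upper bound on the distortion, conditional on preparation following randomisation. Per-protocol PFS shares the problem (about 0.92 at 2 weeks) only under one-sided exclusion. As-treated OS is usually tilted towards the vaccine, but its size and direction depend on crossover share, delay and loss to follow-up, so no single OS figure should be quoted. The PFS sizes assume exponential PFS with a 4-month median and little loss. The primary comparison is not affected; what suffers is the value of these analyses as a check on it. The wording should be corrected.

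**What to change.** In section 2.9, item 4:
- **PFS, as-treated:** model vaccination as a time-dependent exposure, with each patient unvaccinated until the first dose. Alternatively, use a landmark at the planned first-dose date, counted from randomisation and applied identically to both arms.
- **PFS, per-protocol:** apply any exclusion rule symmetrically, so that early progressors are kept or removed in both arms alike.
- **OS:** drop the fixed-group as-treated comparison and rely on the ITT, RPSFT, two-stage and IPCW analyses already planned. Do not substitute a plain time-dependent vaccination model for OS.

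The cost is a change of wording and slightly lower precision in the landmark analysis, which loses the early events of both arms. The time-dependent model needs each patient's first-dose date. The article commits to recording crossover timing; that vaccine-arm first-dose dates are also recorded is a reasonable assumption, but is not stated.

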
## Discussion

3

This clinical trial is the first time that radiotherapy combined with a neoantigen vaccine has been used for phase IV pan-cancer treatment. The response rate of radiotherapy (50, 51) or tumor neoantigen vaccines alone for patients with advanced tumors is only about 30% (52). Although many studies have confirmed that radiotherapy can reshape the immune microenvironment (19), the impact of radiotherapy on tumor neoantigens, the regulation of TIME and the STIE, and the regulatory mechanism of tumor neoantigen vaccines remain unclear. Especially for stage IV patients who are unresectable and have failed multiple lines of treatment, there is an urgent need to conduct clinical trials of radiotherapy combined with tumor neoantigen vaccines to verify the synergistic anti-tumor effect and mechanism. The results will likely provide new treatment opportunities for this population and improve their quality of life.

### Radiotherapy dose

3.1

Different doses of radiotherapy have distinct immunomodulatory effects. Low-dose radiation can reprogram the TIME to promote immune cell infiltration and activation, which can enhance the effectiveness of immune checkpoint blockade (ICB) (53, 54). On the other hand, high-dose radiation, such as 8 Gy administered in 3 fractions, can increase the expression of immunogenic neoantigens, and is known to induce a stronger ICD response. In 4T1 bearing mouse model, this high-dose radiation regimen showed optimal synergy with a neoantigen vaccine (18). This is likely due to the enhanced release of neoantigens and the subsequent activation of both innate and adaptive immune responses. Similar radiation doses have also been shown to enhance the response to ICB (55). Given the importance of radiotherapy dose on TIME, this clinical trial also randomly divided each group into two subgroups: high-dose and low-dose, to explore the immunomodulatory mechanism of radiotherapy dose. We hypothesize that the high-dose regimen will result in stronger ICD, particularly by promoting a more robust release of neoantigens, thereby enhancing the efficacy of neoantigen vaccination. In contrast, while the low-dose regimen may have a more limited direct impact on tumor control, it could still contribute to immune activation, especially when combined with the vaccine.

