**Materials/Methods:**

This is an open-label, multicenter phase II randomized study. The main objective is to evaluate the anti-tumor efficacy of personalized tumor neoantigen peptide vaccines and assess how different radiation doses synergize with vaccination in treating patients with advanced malignant tumors who have progressed after systemic therapy. Patients are stratified by cancer type and randomized 1:1 to receive either placebo with conventional treatment (including high and low dose radiotherapy) or a personalized neoantigen peptide vaccine alongside conventional treatment (including high and low dose radiotherapy). A one-way crossover design is implemented, permitting patients in the placebo arm to transition to the experimental arm upon progression. Clinical outcomes including progression-free survival and objective response rate are assessed both before and after crossover. Key inclusion criteria are as follows: 1) Patients with advanced or recurrent cancers detected by pathology and imaging, who failed first-line treatments; 2) Patients with projected survival ≥3 months and an ECOG score of 0-2; and 3) Patients with at least one predicted high-quality tumor neoantigen.

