0.8028	76	77	153	0.50	4.00	8.00	Equal	24/36	0.10	0.10	0.00	0.00	0.025	0.1972
0.8007	46	47	93	0.40	4.00	10.00	Equal	24/36	0.10	0.10	0.00	0.00	0.025	0.1993
0.8000	481	481	962	0.75	6.00	8.00	Equal	24/36	0.10	0.10	0.00	0.00	0.025	0.2000
0.8003	163	163	326	0.60	6.00	10.00	Equal	24/36	0.10	0.10	0.00	0.00	0.025	0.1997

The sub-group analyses based on high versus low radiation dose are pre-specified exploratory analyses. As there are currently no published studies providing reliable estimates of PFS differences between these sub-groups in the context of neoantigen vaccine therapy, we were unable to perform a dedicated power analysis for the subgroup comparisons. These analyses are intended to be hypothesis-generating and will inform the design of future prospective studies. Additionally, in real-world clinical settings, radiation doses vary considerably among patients, introducing potential confounding effects. To address this, our study design pre-stratified patients into high-dose and low-dose radiation groups rather than allowing radiation prescriptions to vary freely. This approach helps reduce confounding from dose heterogeneity and enhances the interpretability of subgroup findings.

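### The document conflicts on whether radiotherapy dose is randomised, and its only stated dose model does not by itself address the dose-vaccine synergy in the abstract's main objective

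*Protocol article*

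**What the plan says.** **How dose is allocated.** Section 3.1 of the protocol article states that "this clinical trial also randomly divided each group into two subgroups: high-dose and low-dose". Section 2.8 states that "our study design pre-stratified patients into high-dose and low-dose radiation groups rather than allowing radiation prescriptions to vary freely". Section 2.2 describes 1:1 randomisation into the two cohorts, stratified by cancer type and treatment line. It then says only that doses are split into low and high within both cohorts, with no method and no ratio. Section 2.9, item 5, introduces dose with the words "The effect of lab correlates such as RT dose on clinical outcomes of response and time-to-event", to be estimated by logistic and Cox regression.

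**What status the dose question has.** The abstract makes it part of the main objective to "assess how different radiation doses synergize with vaccination". Section 2.1.1, the primary objective, does not mention dose. Section 2.8 calls the high-versus-low comparisons pre-specified but exploratory, without a power calculation. Section 2.2 nevertheless says the design will answer the dose question.

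**How the randomisation strata enter the analysis.** For PFS, section 2.9, item 4, says "Group differences will be compared using the log-rank test". The same item says that cancer type and treatment line will be taken into account. It names cancer type as a Cox covariate, together with unspecified other baseline factors.

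**The concern.** Whether dose is randomised decides what a dose comparison can mean. Section 2.3.1 allows the radiation dose to be adjusted for lesions near critical structures or after previous radiotherapy. If dose level is chosen rather than randomised, it may follow lesion site and treatment history, and a difference between dose groups is then open to confounding. If it is randomised within each arm, the trial is in effect a 2 × 2 factorial, and the dose effect and the vaccine-by-dose interaction are both randomised comparisons.

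The second issue is the match between aim and model. Synergy, and the hypothesis in section 3.1 that the high-dose regimen enhances vaccine efficacy, are statements about an interaction. A reader of the abstract would expect the trial to deliver an answer on it.

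**Working it through.** 1. **Allocation, side by side.** Section 3.1: random, within each arm. Section 2.8: pre-stratified. Section 2.2: split, no mechanism, with randomisation described for the two cohorts only. Section 2.9: a correlate. Only section 3.1, in the Discussion, names a mechanism, and the design section does not confirm it.

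2. **The plan's own event count.** Inputs from section 2.8: "α=0.025 (two-sided), β=0.2"; "The final median PFS was 4 months in the control group and 8 months in the neoantigen vaccine group"; "at least 154 subjects with 77 subjects each group are required"; uniform accrual over 24 months, 36 months in total, loss 0.10. The last row of Table 2 gives 47.7 + 33.9 = 81.6 events.
   - With exponential PFS (hazard λ), exponential loss (hazard η) and h = λ + η, the event probability is (λ/h) × [1 − (e^(−12h) − e^(−36h))/(24h)].
   - Reading the loss as 10% per month, η = −ln 0.9 = 0.105. Control: λ = ln 2/4 = 0.173, probability 0.619, 77 × 0.619 ≈ 47.6 events. Vaccine: λ = ln 2/8 = 0.0866, probability 0.442, 77 × 0.442 ≈ 34.0 events.
   - The total is 81.6, as in Table 2. Schoenfeld's formula requires 80 events for HR 0.50, so the stated design is reproduced.

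3. **Interaction at 81.6 events.** Assume dose is split equally and events D are equal over the four vaccine-by-dose cells. The log hazard ratio at one dose level has variance 4/(D/2) = 8/D. The difference between the two levels has variance 16/D.
   - SE = 4/√81.6 = 0.443.
   - Detectable ratio of hazard ratios (80% power, two-sided 0.05) = exp[(1.960 + 0.842) × 0.443] = exp(1.241) ≈ 3.46, or 1/3.46 = 0.29.
   - Unequal events as in Table 2 (23.85 and 16.95 per cell) give variance 2/23.85 + 2/16.95 = 0.202, SE 0.449 and a ratio of about 3.5.
   - Power is 15% for a ratio of 0.67, 35% for 0.50 and 54% for 0.40. A ratio of 0.50 needs 16 × 2.802²/(ln 0.5)² ≈ 261 events.
   - Range: with no loss at all, 74.7 + 65.5 = 140.2 events would be expected. The detectable ratio is then about 0.39, and power at 0.50 is 54%.

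4. **Why a dose effect is not synergy.** Write log hazard = a·vaccine + b·dose + c·vaccine × dose. Synergy concerns c. A model without the product estimates a dose effect averaged over arms. That effect can be non-zero with c = 0, or near zero when c is large and the effects in the two arms offset each other.

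5. **Why separate subgroup tests do not replace it.** Each dose level has about 40.8 events, which gives about 60% power for HR 0.50 at two-sided 0.05. If the true HR were 0.50 at both levels, exactly one of the two tests would be significant with probability 2 × 0.60 × 0.40 = 48%, suggesting synergy where there is none.

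6. **Strata.** Randomisation uses cancer type and line. The log-rank test is not described as stratified or unstratified, and the Cox model names cancer type but not line.

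**The case against.** The strongest reply is that section 2.8 contrasts its wording with freely varying prescriptions, so it may simply mean assignment to two fixed levels. That is compatible with random allocation, and sections 2.2 and 2.3.1 do not deny it. This stands as a possible reading. It does not remove the need for the design section to state the mechanism, since random allocation of dose appears only in the Discussion.

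Three stronger readings are tempting, and the document does not support them.

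- **That the trial will never test synergy.** A full analysis plan is not shown and may hold an interaction term, and section 2.8 does pre-specify dose subgroup analyses. What can be said is that the only dose model stated here does not by itself address synergy. The low power is already implied by the hypothesis-generating label in section 2.8; what conflicts with it is the abstract.
- **That dose is at once a main, a secondary and an exploratory objective.** Section 2.1.2 concerns safety, immunogenicity, and in-field and distant response. These are different questions from the subgroup comparisons of section 2.8, which are discussed in terms of PFS. The clear mismatch is between the abstract and section 2.8.
- **That the primary test ignores the strata and so loses power.** Section 2.9 says both factors will be taken into account, and its other baseline factors could include line. An unstratified log-rank test after stratified randomisation is conservative, not inflated. Whether stratifying gains or costs power depends on the prognostic spread and the number of strata, and the document gives neither.

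**Conclusion.** The point holds in two parts. First, the document is inconsistent on whether dose is randomised, and this decides whether any dose comparison is causal. Second, the abstract promises an assessment of synergy as part of the main objective, while the body labels the dose analyses exploratory and states a model for the effect of dose only.

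On size, at Table 2's 81.6 events an interaction is detectable with 80% power only at a ratio of hazard ratios of about 3.5 (or 0.29). This assumes an equal dose split, proportional hazards and the normal approximation. Even without any loss to follow-up it would have to be about 0.39. The exploratory label is therefore the right one, and the abstract should carry it.

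The strata issue is secondary: treatment line is not named in the Cox model, and no power loss is shown. The randomised vaccine-versus-placebo comparison on PFS does not depend on any of this.

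**What to change.** Reconcile the abstract with sections 2.2, 2.8, 2.9 and 3.1.

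- **If dose is randomised within arm:** state this and the allocation ratio in section 2.2, and analyse dose as randomised, including where the delivered dose was adjusted. Add a Cox model for PFS with vaccine, dose and vaccine × dose, and report the interaction hazard ratio with its confidence interval. Label it exploratory throughout, including the abstract.
- **If dose is not randomised:** delete the statement of random division in section 3.1 and present dose comparisons as non-causal.
- **Secondary:** name treatment line alongside cancer type, in a few tumour groups fixed in advance, as Cox covariates. This matches the analysis to the randomisation. Power may rise or fall slightly, depending on prognostic spread.

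The cost is a few sentences, one model term and fixing the tumour groups beforehand. Section 3.3 says recruitment began in January 2024, so dose is presumably already being assigned by some mechanism. It should be documented before outcomes by dose are examined.
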